#### ADAPT- ITT, Step 2 (Decision).

Using the information gathered from AIM1 (Assessment). We will form a ten-member team **(THE12**), including invited YGBMSM participants, the GBMSM+NURSES, [name], [name], [name], [name], and [name], led by PI, [name]. THE12 will meet to discuss the results and identify specific intervention activities that should be modified to address ISD and HPART. THE12 will also review to identify evidence-based best actions to address ISD and HPART among YGBMSM for consideration in our decision-making. We will then finalize the specifics of the existing intervention that needs to be adapted to ensure we fully incorporate ISD reduction and HPART/status neutrality focus on the intervention. Considering that the team has diverse persons, mostly GBMSM, with local expertise, we will ensure that the intervention content and adaptation meet the local context of law, religion, language, and HIV communication.

#### ADAPT- ITT Step 3 (Adaptation).

THE12 will conduct initial modifications of the intervention to reflect decisions in Step 2. We will then organize a 3-day mock workshop to administer and theatre test the intervention activities among a sample of YGBMSM+NURSES (n=10) who participated in the previous intervention in Ghana. During the workshop, we will implement the activities (role plays, scenarios, discussions, presentations, games, etc.) that will tackle ISD and HIVST among YGBMSM and HCF staff. As will be done in the intervention, we will implement the HCF components to nurses separately and the YGBMSM component to YGBMSM in the theatre test. We will then collect feedback from GBMSM+NURSES implementers on aspects of the intervention content and delivery that need amendments.

#### ADAPT- ITT Step 4 Production.

THE12 will collate and brainstorm about the experience in the mock intervention workshop. They will review the successful parts of the training for consolidation and devise ways to address the interventions’ challenges or less prosperous areas. We will maintain the study’s focus and be consistent with the literature on HPART, status neutrality, ISD, and relevance to YGBMSM and HCF in Ghana’s slums to ensure we produce a comprehensive yet specific manual to address ISD and increase HPART.

#### ADAPT- ITT Step 5. Topical Expert Review and Step 6. Integration.

We will provide a copy of the *LAFIYA* manual to experts on ISD, HPART, status neutrality, and YGBMSM health in Ghana and SSA for review and feedback. The experts will be asked for feedback on the consistency of the manual to address ISD and to increase HPART among YGBMSM. The experts identified include [name], who led several studies in Ghana and is an expert in ISD and HIV prevention and care among GBMSM. [name] has conducted several studies among HIV key populations and HCWs in Ghana. [name] founded Priorities on Rights and Sexual Health (PORSH), the civil-society organization partners that work with Ghanaian GBMSM and providers. [name] is a community focal person/expert in HIVST and PrEP in Ghana. **[name], MPH, and [name], BSN, are anti-ISD nurses working** with PORSH and Ghana Health Service HCF, offering HIV care to GBMSM. **We will also receive feedback from the Ghana AIDS Control programme, on local program contents and consistency with local HIV prevention and care guidance**. The topical experts will give written feedback and participate in a workshop to discuss pivotal activities and modifications to the local cultural relevance and intervention implementation. THE12 will collate, review and incorporate the feedback to solidify the manual, ask follow-up questions, and discuss areas where the input is unclear to the team.

#### Step 7. Training.

In consultation with the Site PI, the GBMSM+NURSES implementers will select facilitators to deliver the intervention. **For the YGBMSM component**, the facilitators will self-identify as GBMSM and experience participating in previous HIV interventions with GBMSM in Ghana. We expect facilitators to have cultural relatability to topics and the potential anxieties and wariness of the intervention participants. The interventionists will receive a five-day training on group facilitation skills and the LAFIYA intervention from Drs [name] and [name], who have extensive experience training previous facilitators. They would be supported by [name] and [name], who are experts in HIVST, PrEP, and linkage to care; they also facilitated previous interventions among GBMSM in Ghana. **For HCF**, the facilitators will be a combination of intervention HCF staff and GBMSM selected in consultation with HCF management (Ghana health services) and CSOs. The facilitators will receive intense five-day training of trainers on the content of the curriculum and the participatory facilitation skills necessary to deliver it. They then receive five days of on-site coaching at their facilities for the first two pieces of training that they provide. Expert trainers ([name] and [name]) will train the HCW trainers. [name] previously coached [name], who became a star trainer at her HCF and GBMSM levels in NINR’s R01NR019009. They will be supported by [name], [name], and [name], who also participated in previous training. **The team of trainers reflects the GBMSM+NURSES participatory collaboration established throughout this study**. This combination provides a feeling of safety and participant buy-in and allows the opportunity to get perspectives from the other stratum.

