## Methods

### Study design overview.

We aim to adapt and determine the preliminary efficacy of a multilevel status-neutral intervention (LAFIYA) to address HPART adherence among YGBMSM in Ghana’s slums using the following **aims. 1)** Adapt a multilevel intervention to address ISD and HPART using status neutrality among YGBMSM. **2)** Test the preliminary efficacy of the intervention to address ISD and increase HPART adherence using CRT. We will use the ADAPTT-IT framework as a guide to adapt LAFIYA^75^. The framework offers eight steps: (1) Assessment, (2) Decisions, (3) Adaptation, (4) Production, (5) Topical experts, (6) Integration, (7) Training, and (8) Testing. We will use steps 1 to 7 to implement AIM1 and the results from AIM1 to inform AIM2. Aim 1 will produce the intervention manual. AIM 2 will constitute the CRT phase, where we will assess acceptance, feasibility, and appropriateness of the intervention (**implementation outcomes**), the preliminary efficacy of the intervention to reduce ISD (**secondary outcomes**), and increase HPART adherence (**primary outcomes**) among YGBMSM.

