### Implementation of the intervention

#### Implementation procedure.

The facilitators trained in aim one will receive a copy of the manual on delivering each component of the adapted intervention. The intervention will be participatory.

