#### Criteria:

The person must be between 18 to 25 years old, currently identifies as a cis-gender man, have had sex with another man within 8 months before engaging with the recruitment team, and must reside within a slum in the Accra metropolitan area. **Randomization**. When we complete the recruitment and baseline survey, we will stratify peer groups by the number of peer members and give a group ID to each peer group. Within each stratum with an equal number of peers, we will randomly select groups for intervention using simple random sampling. Thus, we will keep equal samples and peer groups between the two study arms.

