#### Randomization.

We will assign 3 HCFs to intervention or control groups based on size; we will first stratify 6 HCFs into groups of two, larger, medium, and smaller sizes, and assign one from each stratum to either arm using SRS.

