### Appraisal of intervention.

#### Data collection.

Participants will complete baseline, 3, 6, and 9 months post-intervention surveys. Trained GBMSM+NURSE partners who collected surveys in our previous studies will conduct the surveys^34,73,74,81,98^. **For YGBMSM**, the data collection location will be at the designated sites (e.g., office of community partners) determined as safe for YGBMSM in Ghana due to their extensive experience working with GBMSM on the grounds in Ghana. **For HCFs**, the data collectors will visit the facilities led by the team leader at the facility to hand over the surveys to providers, who will self-complete them at their convenience. **For PrEP and ART** adherence **biomarkers**, the HCF will provide them with consent from participants during routine check-up visits.

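### Staff of the intervention facilities are picked and trained in Aim 1, but facility randomisation and the healthcare-worker baseline are described only in Aim 2, so allocation may be known before the stigma baseline

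*Protocol article*

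**What the plan says.** The Study design overview divides the work by aim: "We will use steps 1 to 7 to implement AIM1 and the results from AIM1 to inform AIM2". Aim 2 is the cluster-randomised phase.

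Step 7 (Training) is therefore part of Aim 1. For the facility component it states that "the facilitators will be a combination of intervention HCF staff and GBMSM selected in consultation with HCF management". It continues: "The facilitators will receive intense five-day training of trainers on the content of the curriculum", and then "They then receive five days of on-site coaching at their facilities for the first two pieces of training that they provide". The section Implementation procedure, under Aim 2, looks back on this training as finished: "The facilitators trained in aim one will receive a copy of the manual on delivering each component of the adapted intervention".

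Randomisation appears only under Step 8 (Testing/Aim 2). For peer groups the order is explicit: "When we complete the recruitment and baseline survey, we will stratify peer groups by the number of peer members". For facilities the text is "We will assign 3 HCFs to intervention or control groups based on size", followed by the size strata, with no statement of when this happens relative to the HCW survey or to Step 7.

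The survey schedule, also under Aim 2, is "Participants will complete baseline, 3, 6, and 9 months post-intervention surveys". According to Data collection, HCWs fill in the survey themselves. Measures lists change in their stigmatising beliefs and practices as a secondary outcome, and Data analysis estimates the intervention effect through a time-by-group interaction.

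**The concern.** Staff of an intervention facility cannot be chosen until it is known which facilities are in the intervention arm. If that choice is made in Aim 1, and the HCW baseline belongs to Aim 2, then allocation is known at the three intervention facilities before their staff report baseline stigma.

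Two things are at stake for the secondary hypothesis that the intervention reduces the stigma conveyed by facility staff.

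- **Knowledge of allocation.** Stigma is self-reported and open to socially desirable answering. In addition, trainers and peer-led nurses select participants together with facility management (Sampling and recruitment, HCF). If management already knows its arm, both the answers and the choice of staff may differ between arms at baseline. This can affect any sampled worker, trained or not.
- **Early exposure.** If trained facilitators are on the survey list, part of the intervention-arm baseline is measured after exposure. The change from baseline in that arm then looks smaller.

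Because the effect is a time-by-group interaction, any arm difference created at baseline enters the estimate directly.

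**Working it through.** **1. Order of events, set side by side**

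- Facilitators trained: Aim 1 (Study design overview; Step 7; repeated in Implementation procedure).
- Source of HCF facilitators: staff of the intervention facilities (Step 7). Step 8 contrasts intervention facilities with wait-list ones, so the natural meaning is the randomised arm.
- Facilities randomised: Aim 2 (Step 8; Randomization under HCF), no timing given.
- HCW baseline: Aim 2 (Data collection; Measures), no date given.
- Peer groups randomised: Aim 2, after recruitment and baseline (Criteria).

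Step 7 needs the allocation. The allocation and the baseline are described in the next phase. The document as written does not reconcile these.

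**2. The plan's own power figure for this comparison**

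Inputs from Power, HCF: 300 workers (150 per arm), design effect 1.36, effect sizes 0.5 and 0.4. A two-sided 5% level is assumed, since it is stated only for the young men's comparison.

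- Effective n per arm = 150 / 1.36 = 110.3.
- Power = Φ(d × √(n/2) − 1.96), with √(110.3/2) = 7.43.
- d = 0.5: Φ(3.71 − 1.96) = 96.0%.
- d = 0.4: Φ(2.97 − 1.96) = 84.4%.

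The stated 96% and 84% reproduce. They serve here only as the yardstick for the shifts below.

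**3. Size of the early-exposure route**

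Inputs: about 1500 staff in six facilities (Sampling and recruitment, HCF), so 1500/6 = 250 on average; training groups of 15 to 25 (Implementation of the intervention, HCF). Assumptions: the number of facilitators per facility, which is not given; that they are on the survey list; and that a pre-trained worker already shows the full effect d at baseline. Shift = share pre-trained × d.

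*Facilitators only, 2 to 10 per facility:*

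- Share: 2/250 = 0.8% to 10/250 = 4%.
- Shift: 0.008 × 0.4 = 0.003 SD to 0.04 × 0.5 = 0.02 SD.
- At 10 facilitators the visible effect d × (1 − 0.04) is 0.48 or 0.384. Power goes from 96.0% to 94.6%, or from 84.4% to 81.4%.

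*Upper scenario, only if the first two coached trainings also came before baseline:*

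- Staff: 2 × 15 = 30 to 2 × 25 = 50, a share of 12% to 20%.
- Shift at d = 0.5: 0.06 to 0.10 SD.

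The 250 is an average. The facilities are stratified as larger, medium and smaller, so the share would differ between them.

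**4. Size of the allocation-knowledge route**

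No figure can be derived. Nothing in the document says how far answers or selection would move, or in which direction. Random sampling of 300 from about 1500 does not dilute it, because it is not confined to the few trained staff.

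**The case against.** The strongest reply is that no section dates the HCW baseline. The sequence baseline, allocation, facilitator training, delivery contradicts no explicit timing statement about the HCW survey, and it is the order recommended here. A journal article may leave such a schedule to the full protocol. The outcome is secondary in a trial of preliminary efficacy, and effective early training would bias towards the null.

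Part of this stands. A reader might infer that the intervention facilities are already partly treated at baseline and that the HCW baseline is contaminated. The document does not support that as fact:

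- The baseline's position after Step 7 follows only from the aim structure.
- The coaching accompanies the first trainings that facilitators deliver, which is plausibly Aim 2 delivery as set out under Implementation of the intervention. The 12% to 20% of staff is thus a conditional upper scenario.
- The survey sample comes from a list of training participants, and nothing says facilitators are on it. If they are not, their training shifts the baseline not at all.

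What does not stand is that this is merely missing detail. The benign order works only if facility randomisation and the HCW baseline move into Aim 1, against the Study design overview and Step 8. The article also gives the peer groups an explicit safeguard that it does not give the facilities. Bias towards the null describes early training; allocation-aware answering can go either way.

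**Conclusion.** The point holds as a conflict in sequence that should be resolved before the trial starts. Read literally, the article trains intervention-facility staff in Aim 1 and describes facility randomisation and the HCW baseline only in Aim 2, so allocation would be known, and some staff trained, before the stigma baseline.

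The main risk is self-reported answers and participant selection made with allocation known. Its direction is open and its size cannot be derived. The early-exposure route is minor, at most about 0.02 SD and 3 percentage points of power, under the assumptions of 2 to 10 facilitators per facility who are on the survey list. The larger 0.06 to 0.10 SD should be cited only with its condition, that the two coached trainings precede baseline. The issue touches the HCW secondary outcome. It leaves the order of randomisation for the peer groups untouched.

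**What to change.** State one order in both Step 7 and the HCF Randomization section:

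1. Draw the HCW survey sample and complete the HCW baseline in all six facilities.
2. Randomise the facilities within the size strata.
3. Only then select and train the HCF facilitators from the intervention facilities and begin the coached trainings.

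This moves the HCF part of Step 7 to the start of Aim 2, so the Study design overview and Implementation procedure need matching wording. Facilitator training for the young men's component can stay in Aim 1. Also exclude facilitators from the HCW survey list. That exclusion removes the early-exposure route through facilitators but does not cure knowledge of allocation, so it does not replace the ordering.

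The cost is protocol wording and a start some weeks later for HCF facilitator training, with no additional participants or staff. The article reports that recruitment has not begun, so the change can still be made; once facilities are allocated and staff trained, it cannot.

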### STEP 8 (Testing/Aim 2): Test the preliminary efficacy of the intervention to address ISD and increase HPART adherence using CRT Design

We will pilot-test the *LAFIYA* multilevel intervention using a clustered randomized control trial (CRT) with 9 months of waitlist control. Our ultimate aim is to adapt the intervention and preliminary test it for future full-efficacy CRT ^118,119^. Although RCT is primarily used in HIV and behavioral interventions, we find CRT better due to our place-based focus and possible sample contamination. In our previous single arm-pilot (2P30MH062294 −20 // Yale #18–001890, PI, [name]), we identified group sleeping arrangements, observed close-knit networks of GBMSM, and the communal nature of slums as contaminants. We will create two pairs of facilities matched by size and location in each city and randomly assign them to receive the LAFIYA-HCF intervention or the control group. Based on friendship networks, we will create GBMSM groups of 5 to 8 members and randomly assign YGBMSM groups to the LAFIYA-YGBMSM intervention or control group. YGBMSM in the intervention group will be matched with intervention HCF for status-neutral services. The YGBMSM in the waitlist control group will be matched with HCFs in the waitlist control for regular testing, PrEP, and care services. Nurses from the intervention HCF will participate as guest facilitators in one of the LAFIYA-GBMSM sessions. They will use that opportunity to contact YGBMSM to visit their facility for status-neutral care. We will collect 3, 6, and 9 months post-intervention data to measure the preliminary efficacy of the intervention and then implement the intervention in the waitlist group after the completion of data collection. We will use 9 months instead of 6 to allow ample time to measure multiple components, **such as viral suppression,** over a sufficient time. **Our primary hypothesis** is that LAFIYA will increase adherence to HPART among YGBMSM participants. **Our secondary hypothesis** is that the multilevel intervention will reduce the ISD that HCF staff convey and YGBMSM experience in HCFs. It will build the HCF’s capacity to implement status neutrality. We will then **conduct a follow-up qualitative study** (FGDs and IDIs) post-intervention among implementers and participants to evaluate their experiences with the intervention and to seek a more profound understanding or explanations for some of the survey findings.

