## Abstract

**Background:**

While GBMSM constitute less than 2% of Ghana’s population, their HIV prevalence surpasses the national average by more than eightfold, emphasizing the critical need for targeted interventions to improve detection, care linkage, and reduce community transmission. This study seeks to increase HIV testing, Pre-Exposure Prophylaxis (PrEP), and Antiretroviral Therapy (ART) uptake (HPART) among YGBMSM through the adaptation of an evidence-based intervention (LAFIYA).

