**Methodology:**

We will employ the ADAPTT-IT framework to adapt LAFIYA and evaluate its feasibility and effectiveness in addressing intersectional stigma and increasing HPART uptake among YGBMSM residing in Ghanaian slums. In aim 1, we will hold focus groups (n=5) and interviews (n=20) among YGBMSM and two FGDs among GBMSM-led organizations. At the HCF level, we will hold 6 FGDs and interviews (n=20) among nurses. In AIM 2, we will randomly assign 6 healthcare facilities (HCFs) to receive the LAFIYA (n=3) or wait-list control (n=3). Friend groups (cluster) of YGBMSM (N=240) will be assigned to receive LAFIYA (n=120) or a wait-list control (n=120). We will collect 3-, 6-, and 9-months post-intervention data among YGBMSM(n=240) and HCWs(n=300) to measure HPART adherence (primary outcomes), ISD reduction, HIV and status-neutral knowledge (secondary outcomes), and intervention acceptability, appropriateness, and feasibility (implementation outcomes).

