Nonetheless, the uptake of HIV testing, PrEP, and ART (HPART) remains low among GBMSM in Ghana, with many researchers pointing to ISD as a key deterrent^42,45^. In Ghana, ISD towards GBMSM, particularly in the context of HIV, persists despite significant advancements in HIV awareness and advocacy^46,47^. GBMSM also face ISD due to legal, religious, and cultural antagonism, with 90% of Ghanaians against same-sex intercourse^16,48^. Existing evidence suggests a strong association between ISD and low HPART outcomes among this key population in the country^45,46,49–51^. At the intrapersonal level, GBMSM internalizes ISD experiences, develops guilt, shame, etc., and avoid HCFs^45,52–54^.

A mixed-method study in Ghana revealed that 62% of GBMSM respondents reported not testing for HIV in the past 12 months due to ISD^16,55^. Furthermore, our other previous work and others that engaged a section of YGBMSM as part of the generic GBMSM show that YGBMSM have challenges such as low HIV knowledge, ISD, and inadequate connection to care services^19,56–58^. Compared to adults, the ISD faced by YGBMSM also extends to engaging in preventative behaviors. Many cannot engage in HIV prevention conversations or be seen buying or holding a condom due to anti-premarital sex perceptions in Ghana^19,56–58^. Other studies have also reported low PrEP uptake and poor adherence to ART among this key population, with, among other things, stigma being a contributing factor^42,45^.

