### Measures.

#### Demography, HIV testing, and ISD descriptive variables.

We will assess important baseline characteristics for describing the sample, including age, income, gender, education, ethnicity, relationship status, religion, sexual orientation, sexual behavior, HIV knowledge, HIV testing, PrEP and ART readiness, and history. Experiences of ISDs, access, and utilization of health and social services, civic engagement, and neighborhood. **Primary outcomes:** At baseline, 3, 6, and 9 months, we will measure the preliminary efficacy of LAFIYA. We will measure knowledge of HIV and HPART; and willingness to adhere to HPART pre and post-intervention. HPART adherence characteristics (rates, time, mode, location) and biomarkers (Table 2). **Secondary outcomes:** For ISD reduction, we will measure internalized and interpersonal level ISD at baseline and post-intervention surveys among YGBMSM. We will measure HCF-level ISD to understand participant experiences at baseline and changes in HCW stigmatizing beliefs and practices (Table 2). **Implementation outcomes:** We will measure acceptability, appropriateness, and feasibility using expanded Proctors validated measures at pre-immediate and post-intervention surveys at all levels (Table 2)^103^.

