#### Data analysis.

We will use the intent-to-treat (ITT) technique to analyze data. We considered other methods (e.g., per protocol approach), but ITT is less biased since all participants are assessed whether they received the intervention or not. Data collected will be exported to Stata for cleaning and further analysis. Using the Monte Carlo Markov Chain approach based on a multivariate normal distribution of items, we will assess missing patterns in the instrument and impute missing responses with at least 70% of responses. Instruments scores will be calculated with observed and imputed responses. We will summarize the characteristics of participants and calculate Cronbach’s alpha to check internal reliability within scales. We will calculate a mean with a confidence interval for the variables and proportions of responses to the primary and secondary outcome variables. Variables with skewed distribution will be considered for being log-transformed or categorized in ordinal form. We will run inferential statistics such as paired t-test to compare pre-and post-means, McNamara’s test to compare pre-and post-proportions, and correlation analysis to examine the relationship between variables. We will also develop longitudinal models of the outcomes repeatedly measured at baseline, 3, 6, and 9 months post-intervention using a generalized linear mixed effect model (GLMM) with random intercept and peer group, which incorporate ICCs. The GLMM will include time-group interaction to estimate the intervention effect and pre-post changes. The GLMM will consist of all completed observations and drop-outs observed at least once post-intervention. Thus, we will not miss any individuals unless they are entirely missing at all post-intervention periods. Residuals will be assessed for normality assumption and influential outliers diagnosed with leverage, Cook’s distance, and DFFIT. The GLMM will be replaced with logistic and Poisson regressions with random effects when an outcome is binary and count data. We will repeat the same models separately for each site and compare the effect sizes between the sites. When we find any demographics, which are not equivalent between the two interventions, they will be included in the model as covariates. Acceptability, feasibility, and appropriateness will be evaluated with descriptive statistics of the implementation outcomes. **The process defined in AIM**1 will be used to analyze the follow-up qualitative data.

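### The stated question is uptake of testing, PrEP and ART, but the primary hypothesis and outcome are adherence; no uptake outcome is named, and scoring of never-starters is left open

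*Protocol article*

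**What the plan says.** **Uptake as the question.** The title speaks of increasing uptake. Abstract, Background: "This study seeks to increase HIV testing, Pre-Exposure Prophylaxis (PrEP), and Antiretroviral Therapy (ART) uptake (HPART) among YGBMSM". Abstract, Methodology: the trial will "evaluate its feasibility and effectiveness in addressing intersectional stigma and increasing HPART uptake among YGBMSM residing in Ghanaian slums". The Discussion opens with the same goal.

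**Adherence as the endpoint.** The same Methodology paragraph says that data are collected "to measure HPART adherence (primary outcomes), ISD reduction, HIV and status-neutral knowledge (secondary outcomes"). The Study design overview makes adherence the aim and the primary outcome. Under STEP 8 (Testing/Aim 2), the primary hypothesis "is that LAFIYA will increase adherence to HPART among YGBMSM participants".

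**A third version.** The Measures section places knowledge of HIV and HPART and willingness to adhere under primary outcomes, together with "HPART adherence characteristics (rates, time, mode, location) and biomarkers", and refers to Table 2. The abstract lists knowledge as secondary.

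**Who can have a value.** The Introduction says that "the uptake of HIV testing, PrEP, and ART (HPART) remains low among GBMSM in Ghana". The entry criteria do not require current PrEP or ART. Under Appraisal of intervention, Data collection, PrEP and ART biomarkers come from the facilities at routine visits. The Data analysis section commits to intention to treat, and on the mixed model says: "The GLMM will consist of all completed observations and drop-outs observed at least once post-intervention".

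**The concern.** Uptake and adherence are different endpoints with different natural populations. Whether a man tested, or is using PrEP or ART, can be answered for everyone randomised. How well he takes PrEP or ART has a value only if he has started. LAFIYA is meant to move men from not using to using, so starting is part of the effect.

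If adherence is compared only among starters, the LAFIYA group includes men who started because of the intervention and the control group has no counterpart to them. Randomisation no longer protects that comparison. A real gain in use could then appear as a small gain, no difference or a deficit, and the pilot is intended to inform the later efficacy trial. Separately, the question in the title has no named endpoint to answer it.

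**Working it through.** **1. The plan's own power figure.** Inputs from the Power section: 120 men per arm, ICC 0.04, friend groups of 8, effect size 0.50, 5% level (taken as two-sided).

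- Design effect = 1 + (8 - 1) × 0.04 = 1.28.
- Effective n per arm = 120 / 1.28 = 93.75.
- Power = Φ(0.50 × √(93.75/2) - 1.96) = Φ(3.42 - 1.96) = 92.8%; the plan states 92.7%.
- With 108 per arm: effective n = 84.4, power = 90.1%; the plan states 90%.

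The arithmetic reproduces. It is for a scale score and assumes that every man carries one.

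**2. If only a share s of each arm carried a score.** Design effect = 1 + (8s - 1) × 0.04, n = 120s, same effect size:

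| Share scored | n per arm | Design effect | Power |
|---|---|---|---|
| 100% | 120 | 1.280 | 92.8% |
| 80% | 96 | 1.216 | 88.1% |
| 60% | 72 | 1.152 | 79.8% |
| 40% | 48 | 1.088 | 65.1% |
| 30% | 36 | 1.056 | 54.2% |
| 20% | 24 | 1.024 | 40.2% |

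**3. Starters against all randomised.** The documents give no uptake or adherence rates, so these are assumptions: uptake 20% in control and 40% under LAFIYA (24 vs 48 starters); 80% of control starters adherent; the same 20% of men would start under LAFIYA and adhere equally well; the extra 20% adhere at rate a.

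- LAFIYA adherence among starters = (0.20 × 0.80 + 0.20 × a) / 0.40; control = 0.80.
- Adherent over all randomised men, never-starters counted as not adherent: LAFIYA = 0.16 + 0.20a; control = 0.20 × 0.80 = 0.16.

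| a | Starters: control vs LAFIYA | Difference | All randomised: control vs LAFIYA | Difference | Power, all randomised |
|---|---|---|---|---|---|
| 90% | 80% vs 85% | +5 | 16% vs 34% | +18 | 82% |
| 80% | 80% vs 80% | 0 | 16% vs 32% | +16 | 73% |
| 60% | 80% vs 70% | -10 | 16% vs 28% | +12 | 51% |
| 40% | 80% vs 60% | -20 | 16% vs 24% | +8 | 28% |

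Power uses a two-proportion normal approximation with 93.75 effective men per arm. The uptake contrast itself, 20% vs 40%, has about 85% power.

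With uptake of 30% vs 50%, the starters' difference runs from +4 to -16 points, the all-randomised difference again from +18 to +8, and uptake has about 80% power.

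**The case against.** The strongest reply is that starter-only scoring is inferred. The Measures section defers detail to Table 2, which is not in the text at hand and may hold the scoring rule. The Data analysis section commits to intention to treat, and its sentence on the mixed model concerns drop-outs; the next one says that nobody is lost unless missing at every post-intervention visit. HIV testing applies to every man, as do knowledge and willingness, which Measures also lists as primary. The power calculation counts all 240 men. The adherence rates, times, modes and locations to be collected may themselves record whether a man tested or started. And the methods' own aims say adherence, so loose terminology is a possible explanation.

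Much of this stands. A reader might infer that a never-starter cannot be scored, that most of the sample (192 of 240 if 10% of controls and 30% of LAFIYA men start) would have no adherence value, or that the trial would report harm. The documents support none of these as fact: the scoring rule is not shown, those rates are assumed, and 44% HIV prevalence among GBMSM in Accra with no ART coverage figure leaves the share already on treatment unknown. Nor is the direction fixed, since the starters' difference can be positive. In the -10 point case with 24 vs 48 starters, power is only about 13% even ignoring clustering, so an inconclusive result is likelier than significant harm. A reader might also take HPART to be defined as uptake. That rests on where one parenthesis falls; the Introduction attaches the abbreviation to the three services.

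The reply does not remove the conflict between stated question and named endpoint. The intention-to-treat wording also does not settle the scoring: a never-starter whose adherence is blank at every visit would fall under the same missing-at-all-visits exception.

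**Conclusion.** The point holds as an inconsistency in the primary endpoint, with a conditional risk of bias. Established from the text: uptake is the question in the title, abstract and discussion; adherence is the primary hypothesis and named outcome; uptake is named nowhere as an outcome; and knowledge is primary in one place and secondary in another. Conditional on starter-only analysis of PrEP and ART: the comparison is selected after randomisation, and in the illustration it ranges from +5 to -20 points where the all-randomised difference is +18 to +8. Starter-only analysis is a plausible reading, because biomarkers come only from routine visits and the model uses completed observations, but it is not stated. The sizes rest on assumed rates and on carrying the scale-score ICC of 0.04 over to binary outcomes. This should be settled before recruitment, which the article says has not begun.

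**What to change.** Use one primary definition in the abstract, the Study design overview, STEP 8 and Measures, and place knowledge consistently as primary or secondary. Score the primary outcome for every randomised man at each follow-up: tested in the interval (yes/no), and currently on PrEP or ART as appropriate to his HIV status (yes/no). Count never-starters and men who have stopped as no. If adherence is kept as primary, count them as not adherent. Report adherence among starters descriptively, with the number of starters in each arm. The random-effects logistic model already in the Data analysis section fits these outcomes.

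The cost is mainly wording. The sponsor should confirm that current use is asked at every visit, since Measures lists PrEP and ART history among the baseline characteristics; if it is not, a short survey item is needed. The downsides are that a yes/no endpoint is less detailed than an adherence score, and that the published power does not carry over and must be restated. On the illustrative 20% vs 40% rates it would be about 85% for uptake, but between 28% and 82% for adherence over all randomised men.
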